# SYNOPSIS

| **Title** | A Comparative Clinical Study of the Effects of Solifenacin Succinate Treatment in Patients Who Have Frequent Micturition with and without Urgency |
| --- | --- |
| **Sponsor** | Astellas Korea |
| **Principal**  **Investigator** | [name], Asan Medical Center Department of Urology |
| **Objectives** | **1. Primary objective**  To compare changes in micturition frequency on 3-day voiding diary from baseline to week 12- of treatment with solifenacin succinate in group 1 (frequency without urgency) and group 2 (frequency with urgency).  **2. Secondary objectives**   - To compare improvements in the patient’s perception of bladder condition (PPBC) at week 12 of treatment with solifenacin succinate. - To compare improvements in the OAB symptom score (OABSS) at week 12 of treatment with solifenacin succinate. - To compare percent changes in mean void volume at week 12 of treatment with solifenacin succinate. - To compare percent changes in maximum bladder capacity at week 12 of treatment with solifenacin succinate. - To assess patient satisfaction by the Benefit, Satisfaction and Willingness to Continue (BSW) questionnaire at week 12 of treatment with solifenacin succinate. - To identify pre-treatment factors (age, sex, baseline episodes of frequency, education level, etc) associated with frequency improvement in group 1 |
| **Evaluation** | **Primary efficacy endpoint**   - 3-day voiding diary   **Secondary efficacy endpoints**   - Patient’s Perception of Bladder Condition (PPBC) questionnaire - Overactive bladder symptom score (OABSS) - Benefit, Satisfaction and Willingness to Continue (BSW) questionnaire   **Safety endpoints**   - Adverse events - maximum flow rate and post-void residual urine volume |
| **Design** | Multicenter, comparative, open-label phase IV trial  Non-inferiority study  Hypothesis: The effect of solifenacin is not inferior in patients with frequency only to others with both frequency and urgency. |
| **Study drug** | Solifenacin Succinate (Vesicare®) |
| **Inclusion Criteria** | 1. Male or female aged ≥ 18 years 2. Micturition frequency ≥ 8/24 hrs 3. Grouped based on voiding diary data:   For group 1, no urinary urgency (1 or 2 on 5-point urgency scale)  For group 2, ≥ 2 urinary urgency episodes per day (3 to 5 on 5-point urgency scale)   1. Continuous presence of the symptoms above for more than 3 months |

| **Study population and Number of study centers** | Expected number of subjects enrolled: 286 patients  Number of subjects expected to complete the study : 256 patients (128 in each group), considering a10% drop-out rate  Duration of medication: 3 months  Number of centers: 9 centers |
| --- | --- |
| **Statistical analysis** | Efficacy analysis will be performed in FAS and PP sets, whereas safety analysis will be conducted in those patients who have taken the study drug at least once.  - Primary efficacy assessment  A t-test will be used to compare changes in frequency of urination (from baseline to the end of the study) between study groups on the voiding diary (see Annex 1) and calculate a 95% confidence interval for the difference between the groups. Further analysis, if necessary, will be conducted with a generalized linear model in order to correct heterogeneity between the groups.  - Secondary efficacy assessment  Secondary efficacy endpoints (i.e., PPBC, OABSS and BSW) will be analyzed using the the Wilcoxon signed-rank sum test or paired t-test for continuous data and the McNemar test for categorical data. If necessary, a mixed effect model or generalized estimation equation will be used as an analysis tool to test the difference between study groups. |
| **Expected study duration** | Patient screening begins in February 2009.  The last patient enrollment is completed by the end of June 2009. |

# Study Schedule

|  | V0  (Days -21 to 0) | V1  (Day 0) | V2  (Week 4 ± 7 days) | V3  (Week 12 ± 7 days) |
| --- | --- | --- | --- | --- |
| (baseline) * | |
| Informed consent | **●** |  |  |  |
| Demographics | **●** |  |  |  |
| Medical history, associated  diseases | **●** |  |  |  |
| Laboratory test:  CBC  Chemistry**  Urinalysis  PSA (only in male)*** | **●**  **●**  **●**  **●** |  |  |  |
| Voiding diary dispensed | **● ****** | **●** | **●** |  |
| Voiding diary collected |  | **●** | **●** | **●** |
| PPBC | **●** |  | **●** | **●** |
| OABSS | **●** |  | **●** | **●** |
| Flow rate (Uroflowmetry) | **●** |  |  | **●** |
| Residual urine (Bladder scan) | **●** |  |  | **●** |
| BSW questionnaire |  |  |  | **●** |
| Prescription |  | **●** | **●** |  |
| Compliance |  |  | **●** | **●** |
| Adverse events |  |  | **●** | **●** |
| Concomitant medications | **●** | **● ******* | **●** | **●** |

Intervals between different visits: ± 7 days

* Screening tests should be performed and confirmed prior to prescription at V1.

** Chemistry: AST, ALT, BUN, Cr, ALP, T-bil

*** PSA leves should be measurements within the last 3 months (replaceable by data from other institutions).

**** Voiding diary should be kept for 3 days prior to V1, V2 and V3.

***** Any prohibited drugs must not have been taken for at least 2 weeks prior to V1.

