4. Any condition that is a contraindication for anticholinergic treatment, including uncontrolled narrow-angled glaucoma, urinary retention or gastric retention
5. Symptomatic acute urinary tract infection (UTI) during the run-in period
6. Recurrent UTIs defined as having been treated for symptomatic UTIs > 4 times in the last year
7. Diagnosed or suspected interstitial cystitis
8. Uninvestigated hematuria or hematuria secondary to malignant disease.
9. Clinically significant bladder outlet obstruction defined by clinical symptoms and in the investigator’s opinion according to the local standard of care (residual urine > 100 ml)
10. Marked cystocele or other clinically significant pelvic prolapse.
11. Treatment within 14 days prior to randomization, or expected to initiate treatment during the study, with:
    - Any anticholinergic drug other than the randomized trial drug
    - Any drug treatment for overactive bladder. Estrogen treatment started more than 2 months prior to inclusion is allowed.
12. On an unstable dosage of any drug with anticholinergic side effects, or expected to start such treatment during the study
13. Receipt of any electrostimulation or bladder training within 14 days before randomization, or expected to start such treatment during the study
14. Use of an indwelling catheter or practicing intermittent self-catheterization
15. Use of any investigational drug within one month preceding the start of the study
16. Chronic constipation or history of severe constipation
17. Pregnant or nursing women
18. Sexually active females of childbearing potential not using reliable contraception for at least one month prior to the start of the clinical trial and not agreeing to use such methods during the entire study period. Reliable contraceptive methods are defined as intrauterine devices (IUDs), combination type contraceptive pills, hormonal implants, double barrier method, injectable contraceptives and surgical procedures such as tubal ligation or vasectomy.
19. Presence of bladder cancer or prostate cancer
20. Patients on treatment with potent CYP3A4 inhibitors, such as cyclosporine, vinblastine, macrolide antibiotics (e.g. erythromycin, clarithromycin and azithromycin) or antifungal agents (such as ketoconazole, itraconazole and micronazole).
21. Presence of any neurological disease
22. Presence of any psychological disease
23. Any other conditions which, in the investigator’s opinion, make the patient unsuitable for inclusion

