4.6.1 Prohibited concomitant medications

1. Other anticholinergics
2. Tricyclic antidepressants

Subjects who have discontinued any of these medications must have a wash-out period of 14 days and can be enrolled in the study.

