# **6. Evaluation of the Study Drug**

All efficacy endpoints, except the BSW questionnaire, are compared with baseline.

6. 1. Primary efficacy endpoint

- Changes in micturition frequency on the voiding diary (Appendix 1) (from baseline to end of study)

6. 2. Secondary efficacy endpoints

- PPBC (changes from baseline to week 12)
- OABSS (changes from baseline to week 12)
- BSW questionnaire at week 12

6. 3. Safety endpoints

General clinical safety will be assessed based on data on spontaneously reported adverse events at each visit. To this end, subjects will be asked: “Since last visit*,* have you had any unusual symptoms or any health problems you had never experienced before?”

- Adverse events
- Changes in maximum flow rate (MFR) measured by uroflowmetry (from baseline to week 12)
- Changes in post-void residual (PVR) urine volume assessed by bladder scan (from baseline to week 12)

According to the recommendations of the International Consultation on BPH, the PSA will be measured at baseline. Normal laboratory ranges will be provided in the CRF.

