# **7. Practical Conduct of the Study**

7. 1.Visit 0 (days -21 to 0)

- An oral explanation of the clinical trial to subjects.
- Dating and signing of the informed consent form by subjects
- Collection of necessary information including demographics, disease history, clinical history and associated conditions and relevant concomitant medications.
- Physical examinations including a digital rectal exam in male subjects.
- Laboratory tests: Urinalysis, CBC, chemistry and serum PSA (only in male subjects)
- PPBC and OABSS assessments
- Uroflowmetry and residual urine assessment
- A voiding diary is explained and given to each subject.
- Identification of concomitant medications

7. 2.Visit 1 (day 0)

- Laboratory test results are confirmed.
- Subjects for the clinical trial are selected based on the inclusion and exclusion criteria after an evaluation of their voiding diaries.
- Subjects are prescribed one Vesicare 5 mg tablet to take before sleep for four weeks. The tablet should not be chewed, divided or crushed.
- Concomitant medications are identified.
- The voiding diary is given to each subject.

7. 3. Visit 2 (week 4)

Visit 2 will take place four weeks after the inclusion visit (or if necessary, within seven days before or after the theoretical date).

- Adverse events are identified.
- The date when each subject took the study drug is confirmed.
- The voiding diary is evaluated.
- The PPBC and OABSS questionnaires are evaluated.
- Subjects are prescribed one 5 or 10mg Vesicare 5 mg or 10 mg tablet to take before sleep for eight weeks. The tablet should not be chewed, divided or crushed. Dose escalation to 10 mg is determined after consultation between the investigator and subjects.
- Concomitant medications are identified.
- The voiding diary is given to each subject.

7. 4. Visit 3 (week 12)

Visit 3 will take place eight weeks after the inclusion visit (or if necessary, within seven days before or after the theoretical date).

- Adverse events are identified.
- The date when each subject took the study drug is confirmed.
- The voiding diary is evaluated.
- The PPBC and OABSS questionnaires are evaluated.
- Concomitant medications are identified.
- Uroflowmetry and residual urine assessment
- Patient satisfaction with the study drug is assessed by the BSW questionnaire.

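### The only pre-dose PPBC, OABSS, flow rate and residual urine are taken at V0, but the 14-day wash-out counts back from V1, so some of these baselines may be on-drug

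*Protocol*

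**What the plan says.** The Study Schedule marks PPBC, OABSS, flow rate and residual urine at V0 (days -21 to 0) and leaves V1 empty for all four. Section 7.1 lists "PPBC and OABSS assessments" and "Uroflowmetry and residual urine assessment" under Visit 0, and section 7.2 does not repeat them at Visit 1. The questionnaires next appear at V2; flow rate and residual urine next appear at V3.

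Sections 6.2 and 6.3 define all four as changes from baseline to week 12. V0 is therefore the only source of the baseline value.

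Section 4.6.1 lists "Other anticholinergics" and tricyclic antidepressants as prohibited, but admits patients who stop them: "Subjects who have discontinued any of these medications must have a wash-out period of 14 days and can be enrolled in the study". A Study Schedule footnote sets the reference point: "Any prohibited drugs must not have been taken for at least 2 weeks prior to V1". It is attached to the V1 entry for concomitant medications, not the V0 entry. Exclusion criterion 11 also uses 14 days, counted from a randomization that this trial does not have; in practice that means V1.

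The voiding diary is treated differently: the schedule ties it to the 3 days before V1, V2 and V3.

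**The concern.** The screening window is longer than the wash-out, and four baselines sit at its early end. Consent and the first review of concomitant medication both take place at V0, so a patient who stops an anticholinergic in order to join would be expected to stop at or after that visit. For that patient the diary baseline is off drug, while the other four baselines may reflect the earlier treatment.

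An on-drug PPBC or OABSS baseline may already look improved, leaving less room for change on solifenacin. A residual urine already raised by the earlier drug would hide a rise during the study. PPBC and OABSS carry two of the secondary objectives, and flow rate and residual urine are the only measured safety variables with a planned change from baseline.

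**Working it through.** The plan gives no figure of its own for this point, so the check is a timeline followed by a bias expression.

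**Inputs from the protocol**
- V0: day -21 to day 0 (Study Schedule, section 7.1).
- Drug-free period: at least 14 days, counted back from V1 (Study Schedule footnote).
- Baseline diary: the 3 days before V1 (Study Schedule footnote).

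**Step 1: drug-free time at V0.** The last permitted prohibited dose is on day -14. If V0 falls v days before V1, the guaranteed drug-free time at V0 is max(0, 14 - v).

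| V0 on day | Guaranteed drug-free days |
| --- | --- |
| -21 | 0 |
| -18 | 0 |
| -14 | 0 |
| -10 | 4 |
| -7 | 7 |
| -3 | 11 |
| 0 | 14 |

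The window exceeds the wash-out by 21 - 14 = 7 days. A patient who stops at V0 itself must have V0 at day -14 or earlier, which is the part of the window with no guaranteed drug-free time.

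**Step 2: the diary.** It begins 3 days before V1, so at least 14 - 3 = 11 drug-free days have passed. The gap at V0 does not reach it.

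**Step 3: effect on mean change.** Let p be the share of a group still on drug, or not fully washed out, at V0, and e the effect of the earlier drug still present in the measure at V0.
- Within a group, mean improvement is understated by p × e.
- The group 1 minus group 2 difference in improvement shifts by p2 × e2 - p1 × e1.

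The protocol gives neither p nor e. For illustration only, assume p between 10% and 30% and the same e in both groups:
- within a group: 0.1e to 0.3e;
- between groups, equal shares: 0;
- between groups, 10% in group 1 and 30% in group 2: (0.30 - 0.10)e = 0.2e, in favour of group 1;
- between groups, shares reversed: -0.2e, in favour of group 2.

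**Step 4: after the change.** A measurement at V1 before the first dose has at least 14 drug-free days in every patient. The sample size is unchanged.

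**The case against.** Several points on the other side have weight.

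- **No affected patients may exist.** Section 4.6.1 also fits patients who stopped well before V0, and the share on drug at V0 is not given. This stands: a reader might infer that the four changes are biased, but the text supports only that they may be, in patients who are washing out.
- **Entry criteria limit the effect.** Symptoms must have been continuously present for more than 3 months, so well-controlled patients on an anticholinergic should not qualify. This reduces the earlier drug's effect at V0. Partial responders can still enter.
- **V0 can be late.** The window runs to day 0, so a site could take the measurements after the wash-out. The protocol permits this but does not require it.
- **Prior use is recorded and adjustment is foreseen.** Concomitant medications are collected at V0 and V1, and section 10.4.1 provides for correcting efficacy analyses when the groups differ. The record is useful, but adjustment does not recover an off-drug baseline. Section 10.4 also plans paired tests for the secondary endpoints, where understatement arises even with equal prior use.

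A stronger reading is that the bias runs between the groups and favours group 1, because section 1 describes antimuscarinics as standard OAB treatment and group 2 is the OAB group. That is plausible but not established: the same section argues that many patients with frequency alone may be OAB cases who would benefit from these drugs, so prior use in group 1 is plausible too. A figure in OABSS points would rest entirely on assumed shares and effects.

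**Conclusion.** The timing gap is certain from the text: nothing requires a patient to be off prohibited drugs when the only pre-dose PPBC, OABSS, flow rate and residual urine are recorded, and guaranteed drug-free time is zero for V0 at days -21 to -14. For patients washing out an anticholinergic, PPBC and OABSS improvement may be understated and a rise in residual urine masked. This assumes that some such patients enrol and that the earlier drug still acts on the measure at V0.

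The size cannot be derived from the protocol: it is p × e within a group. Between groups the bias is zero if shares and effects are equal, and otherwise of unknown size and direction. A reader might infer that the non-inferiority conclusion is at risk. It is not, on this ground, because the primary endpoint uses the diary kept just before V1. The point concerns two secondary and two safety measures in a subset of unknown size, and merits correction mainly because the remedy is cheap.

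**What to change.** 1. Administer PPBC and OABSS at V1, before the first dose, and name those values as the baseline for change to week 12. V1 is an existing visit, at which the diary is already collected.
2. For patients who need a wash-out, schedule the single baseline flow rate and residual urine measurement after it is complete. It must still precede prescription at V1, because residual urine also enters exclusion criterion 9.
3. If flow rate and residual urine stay at V0, report their change with and without patients who were on a prohibited drug at V0, using the concomitant medication record already taken at that visit. This shows how far the result depends on those patients but does not give them an off-drug baseline.

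The cost is a small change in visit logistics: two short questionnaires move to V1, and one uroflow and bladder scan are timed later for washed-out patients. No treatment rule and no sample size changes.

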# **1. Introduction**

Antimuscarinic drugs have been a mainstay of treatment for overactive bladder (OAB) which is defined as urgency, with or without urge incontinence, usually with frequency and nocturia by ICS. Although urgency is a key symptom of OAB, frequency is reported as one of the most common and bothersome symptoms in OAB patients, as found in IMPACT and STARGATE studies.

This urinary frequency may be caused by many different factors including urgency, cystitis, polyuria, polysypsia, neuropsychiatric factors and habitual factors. Urgency is a very difficult condition for patients and doctors to perceive and describe. Some patients cannot discriminate urgency from normal urge. Some should go to the toilet because of the discomfort (not pain) on suprapubic area before they feel urgency, in which case they deny the presence of urgency. In this sense, all or many patients who have urinary frequency without urgency may be classified as OAB cases, if cystitis, poyuria and neuropsychiatric factors are not taken into consideration. Consequently, we think that anticholinergics can improve symptoms in most patients who have urinary frequency without urgency.

# **2. Study Objectives**

To examine the effects of solifenacin succinate treatment in patients who have frequent micturition with or without urgency.

2. 1. Primary objective

To compare changes in micturition frequency on 3-day voiding diary from baseline to week 12 of treatment with solifenacin succinate between group 1 (frequency without urgency) and group 2 (frequency with urgency)

2. 2. Secondary objectives

- To compare improvements in the PPBC at week 12 of treatment with solifenacin succinate.

- To compare improvements in the OABSS at week 12 of treatment with solifenacin succinate.

- To compare percent changes in mean void volume at week 12 of treatment with solifenacin succinate.

- To compare percent changes in maximum bladder capacity at week 12 of treatment with solifenacin succinate.

- To assess patient satisfaction by the BSW questionnaire at week 12 of treatment with solifenacin succinate.

- To identify pre-treatment factors (age, sex, baseline episodes of frequency, education level, etc) associated with frequency improvement in group 1.

# **3. Description of the Study**

This study is an open-label, multi-center, observational, comparative trial conducted for three months by nine urologists in South Korea.

This study is also a non-inferiority study hypothesizing that the effect of solifenacin is not inferior in patients with frequency only to others with both frequency and urgency.

Principal investigator: [name], University of Ulsan Asan Medical Center

Co-investigator: [name] [name], Inha University Hospital

Co-investigator: [name] [name] (co-investigator), Keimyung University Dongsan Medical Center

Co-investigator: [name] [name], Korea University Hospital

Co-investigator: [name] [name], Pusan National University Hospital

Co-investigator: [name] [name], Daegu Catholic University Hospital

Co-investigator: [name], Samsung Medical Center, Sungkyunkwan University

Co-investigator: [name], Chungnam National University Hospital

Co-investigator: [name] [name], Chonnam National University Hospital

In this study, the screening period is from week 0 to week 3. Patients included in the trial will receive one tablet of solifenacin succinate (5 mg or 10 mg) for a period of three months.

This study will involve four planned visits: pre-inclusion visit (V0), inclusion visit (V1), 1 intermediate visit (V2, 4-week intervals) and end-of-study visit (V3, week 12).

If needed, visits may take place within 7 days before or after the theoretical dates calculated from V1.

Demographics include body weight, age, sex, education level, occupation and parity (for female only). Patients are asked to keep a 3-day voiding diary at baseline and at weeks 4 and 12 after initiation of treatment.

Patients are divided into two groups: group 1 (frequency without urgency) and group 2 (frequency with urgency). Both of the groups receive solifenacin succinate over a period of 12 weeks.

- At the beginning, patients receive solifenacin succinate 5 mg.

- At week 4, they can have the dose escalated to 10 mg after consultation with the investigator.

- If there are patients who are not able to withstand the new dose after dose escalation, it can be reduced back.

Uroflowmetry and residual urine measurement will be performed at baseline and week 12.

Patients will be asked to complete the PPBC and OABSS questionnaires at baseline and at weeks 4 and 12 of treatment. At the end of the study, they will be asked to complete the BSW questionnaire.

# **4. Selection of Patients**

4. 1. Planned number of patients

This study will include 286 patients recruited in South Korea, and at least 256 of them are expected to complete our 3-month medication course.

4. 2. Number of patients per center

Each study center should enroll at least 32 patients, 29 of whom should complete the study.

4. 3. Study groups

Based on voiding diary data, subjects are assigned to one of two groups: Group 1 includes patients who have frequency without urgency, while group 2 consists of those who have frequency with urgency (overactive bladder patients).

Patients in group 1 (frequency-only group) are those with a mean urinary frequency of ≥ 8 micturitions per 24 hours for three days and a score of 1-2 on the 5-point urgency scale. Group 2 (OAB group with frequency and urgency) includes patients who experience on average ≥ 8 micturitions per 24 hours for three days and ≥ 2 urgency episodes per 24 hours (or 3-5 on the 5-point urgency scale) they belong to group 2.

4. 4. Inclusion criteria

Subjects must meet all of the following inclusion criteria to be eligible for enrollment in this study:

Male or female aged  18 years

For group 1

- Urinary frequency  8 micturitions per 24 hours
- No urgency on voiding diary (1 or 2 on 5-point urgency scale)

For group 2

- Urinary frequency of  8 micturitions per 24 hours
- ≥ 2 episodes of urgency on average per day on voiding diary (3-5 on 5-point urgency scale)

Continuous presence of the symptoms above for more than 3 months.

Ability and willingness to complete the voiding diary and questionnaires accurately

Capable of understanding and having signed the informed consent form after full discussion of the research nature of the treatment and its risks and benefits

4. 5. Exclusion criteria

Patients presenting with any of the following will be excluded from this study:

1. Clinically significant stress incontinence as determined by the investigator or confirmed by a cough provocation test for female patients.
2. Total daily urine volume of > 3000 ml as verified on the voiding diary before randomization
3. Significant hepatic or renal disease, defined as having twice the upper limit of the reference ranges for serum concentrations of aspartate aminotransferase (AST [SGOT]), alanine aminotransferase (ALT [SGPT]), alkaline phosphatase or creatinine
4. Any condition that is a contraindication for anticholinergic treatment, including uncontrolled narrow-angled glaucoma, urinary retention or gastric retention
5. Symptomatic acute urinary tract infection (UTI) during the run-in period
6. Recurrent UTIs defined as having been treated for symptomatic UTIs > 4 times in the last year
7. Diagnosed or suspected interstitial cystitis
8. Uninvestigated hematuria or hematuria secondary to malignant disease.
9. Clinically significant bladder outlet obstruction defined by clinical symptoms and in the investigator’s opinion according to the local standard of care (residual urine > 100 ml)
10. Marked cystocele or other clinically significant pelvic prolapse.
11. Treatment within 14 days prior to randomization, or expected to initiate treatment during the study, with:
    - Any anticholinergic drug other than the randomized trial drug
    - Any drug treatment for overactive bladder. Estrogen treatment started more than 2 months prior to inclusion is allowed.
12. On an unstable dosage of any drug with anticholinergic side effects, or expected to start such treatment during the study
13. Receipt of any electrostimulation or bladder training within 14 days before randomization, or expected to start such treatment during the study
14. Use of an indwelling catheter or practicing intermittent self-catheterization
15. Use of any investigational drug within one month preceding the start of the study
16. Chronic constipation or history of severe constipation
17. Pregnant or nursing women
18. Sexually active females of childbearing potential not using reliable contraception for at least one month prior to the start of the clinical trial and not agreeing to use such methods during the entire study period. Reliable contraceptive methods are defined as intrauterine devices (IUDs), combination type contraceptive pills, hormonal implants, double barrier method, injectable contraceptives and surgical procedures such as tubal ligation or vasectomy.
19. Presence of bladder cancer or prostate cancer
20. Patients on treatment with potent CYP3A4 inhibitors, such as cyclosporine, vinblastine, macrolide antibiotics (e.g. erythromycin, clarithromycin and azithromycin) or antifungal agents (such as ketoconazole, itraconazole and micronazole).
21. Presence of any neurological disease
22. Presence of any psychological disease
23. Any other conditions which, in the investigator’s opinion, make the patient unsuitable for inclusion

4. 6. Use of concomitant medications

